## Abstract

**Introduction:**

Indigenous peoples who have experienced colonisation or oppression can have a higher prevalence of alcohol-related harms. In Australia, Aboriginal Community Controlled Health Services (ACCHSs) offer culturally accessible care to Aboriginal and Torres Strait Islander (Indigenous) peoples. However there are many competing health, socioeconomic and cultural client needs.

**Methods and analysis:**

A randomised cluster wait-control trial will test the effectiveness of a model of tailored and collaborative support for ACCHSs in increasing use of alcohol screening (with Alcohol Use Disorders Identification Test-Consumption (AUDIT-C)) and of treatment provision (brief intervention, counselling or relapse prevention medicines).

**Setting:**

Twenty-two ACCHSs across Australia.

**Randomisation:**

Services will be stratified by remoteness, then randomised into two groups. Half receive support soon after the trial starts (intervention or ‘early support’); half receive support 2 years later (wait-control or ‘late support’).

**The support:**

Core support elements will be tailored to local needs and include: support to nominate two staff as champions for increasing alcohol care; a national training workshop and bimonthly teleconferences for service champions to share knowledge; onsite training, and bimonthly feedback on routinely collected data on screening and treatment provision.

**Outcomes and analysis:**

Primary outcome is use of screening using AUDIT-C as routinely recorded on practice software. Secondary outcomes are recording of brief intervention, counselling, relapse prevention medicines; and blood pressure, gamma glutamyltransferase and HbA1c. Multi-level logistic regression will be used to test the effectiveness of support.

**Ethics and dissemination:**

Ethical approval has been obtained from eight ethics committees: the Aboriginal Health and Medical Research Council of New South Wales (1217/16); Central Australian Human Research Ethics Committee (CA-17-2842); Northern Territory Department of Health and Menzies School of Health Research (2017-2737); Central Queensland Hospital and Health Service (17/QCQ/9); Far North Queensland (17/QCH/45-1143); Aboriginal Health Research Ethics Committee, South Australia (04-16-694); St Vincent’s Hospital (Melbourne) Human Research Ethics Committee (LRR 036/17); and Western Australian Aboriginal Health Ethics Committee (779).

**Trial registration number:**

ACTRN12618001892202; Pre-results.

Strengths and limitations of this studyThis large cluster randomised controlled trial provides the power to test whether a model of support for Aboriginal and Torres Strait Islander primary care services can increase rates of alcohol screening and treatment provision.The protocol has been designed to be compatible with cultural context and to integrate western knowledge with the expertise and holistic approaches of these services.The use of regular data feedback and nomination of service champions offers the services an opportunity to be involved in ongoing quality improvement on alcohol care.The resultant study will be able to use routinely collected outcome data but this relies on the accurate recording of screening and alcohol care provided to clients.

## Introduction

Globally, alcohol is the leading cause of loss of healthy life years for people between the ages of 15 and 49.^1^ Indigenous peoples dealing with colonisation and oppression can be at higher risk of mental illness and harms from alcohol.^2^ In Australia, the proportion of Aboriginal and Torres Strait Islander (Indigenous) people who drink alcohol is less than non-Indigenous people.^3^ However, Indigenous Australians are 2–8 times more likely to be hospitalised for alcohol-related conditions^4^ and nine times more likely to die from alcohol-related harms.^5^ This directly impacts on the health gap between Indigenous and non-Indigenous Australians.^4^ These increased risks and harms from drinking can be related to experiences of trauma, grief, poverty and cultural dispossession, resulting in increased mental illness, trans-generational trauma and lower life expectancy.^2 4 6^ The lack of community autonomy and access to culturally appropriate treatment services also contribute.^4^

Early detection of unhealthy drinking (ie, of hazardous, harmful or dependent alcohol use)^7 8^ plays a key role in reducing the overall burden of alcohol conditions, particularly before people develop health problems or social impacts such as incarceration related to alcohol use.^9–11^ Internationally, alcohol screening and brief intervention approaches have been found to be cost-effective in reducing unhealthy drinking, particularly for those who are not dependent on alcohol.^9 12^ However across Australian primary care settings, screening and brief intervention for unhealthy drinking are not always standardised,^13^ informed by Australian National Health and Medical Research Council (NHMRC) drinking guidelines,^14^ or systematically conducted. It is estimated that 50%–70% of people with unhealthy drinking go undetected in Australian primary care.^15^ Similarly only 57% of attendees were screened for unhealthy drinking in four Indigenous primary care settings in Queensland, Australia (in 2007).^16^ Also, when alcohol dependence is present, pharmacological treatments to reduce risk of relapse are not regularly prescribed in primary healthcare.^17–19^

Culturally specific healthcare services that are led and delivered by Indigenous peoples can have a key role in improving quality of healthcare and treatment access.^20^ Aboriginal Community Controlled Health Services (ACCHSs) provide accessible and culturally appropriate healthcare to Indigenous communities across Australia. Each ACCHS has its own holistic service delivery model for the communities that they serve.^20^ As with mainstream (general population) services, knowledge and practice of screening and brief intervention vary between and within Indigenous primary care services.^13 21 22^ Some ACCHSs have an alcohol and other drug (AOD) worker or team, or links with external AOD specialists/services. Others may have no specific AOD expertise and health practitioners may lack confidence in delivering alcohol care (ie, screening, brief intervention, counselling or medicines). Prior to 2017, the Australian government had asked ACCHS staff to record clients’ alcohol use as ‘safe’ or ‘unsafe’, ‘non-drinker’ or ‘ex-drinker’.^22^ However health practitioners may or may not have known current drinking guidelines or have applied these to assess the risk.

To increase standardisation of alcohol screening in ACCHSs, in July 2017 the use of the Alcohol Use Disorders Identification Test-Consumption (AUDIT-C) was added as a national key performance indicator for ACCHSs.^23^ AUDIT-C^24^ is a 3-item screening tool, comprised of the first three questions of the 10-item AUDIT.^25^ This short form has been shown to have good sensitivity and specificity in comparison to the full AUDIT.^24^ Several studies suggest that AUDIT-C is valid in Indigenous primary care settings, though further study into culturally appropriate delivery is suggested.^26–28^

Internationally, research suggests that support can help primary care services increase implementation of alcohol screening and brief intervention^29^ or provision of pharmacotherapies for relapse prevention in alcohol dependence.^19^ Support which is multi-faceted, and targets several areas of a health service seems particularly promising.^29^ For example the approach may target not just doctors, but other professionals, clients, and organisational systems.^29^ Continuing quality improvement approaches may offer sustainable benefit, including in ACCHSs.^30^ However there have been very few studies of culturally relevant support models for ACCHSs in alcohol care,^21 30^ with even fewer conducted by Indigenous researchers.

This paper outlines the trial protocol for testing if a model of support can assist ACCHSs to integrate the mainstream evidence base on alcohol care with their own cultural and clinical expertise. The use of an inactive control group can be challenging on ethical and partnership grounds, particularly for vulnerable communities. In contrast, a wait-control design allows support to be delivered to all participating ACCHSs.

## Aims

This trial aims to assess if a model of tailored and collaborative support for ACCHSs can result in increased uptake of evidence-based screening and treatment for unhealthy alcohol use (ie, drinking above recommended limits). This service-wide model of support will be designed to build on services’ existing strengths (figure 1).

**Figure 1 F1:**
[figure not shown]
Project principles—embedding mainstream evidence into a cultural care approach.

## Methods

### Overview

A cluster randomised trial will test the effectiveness of a model of tailored and collaborative support to increase the use of AUDIT-C and evidence-based treatment in ACCHSs compared with care as usual. Culturally relevant supports will be offered with the aim of increasing staff skills and capacity to develop, refine and deliver systems for alcohol care. These supports will be based on current evidence and be in-line with services’ cultural-care practices. Twenty-two ACCHSs will be recruited across Australia. Services will be randomised into two arms, an early support (intervention) and a late support (wait-control) arm (figure 2).

**Figure 2 F2:**
[figure not shown]
Flow diagram for the trial.

The support provided will contain eight core elements (table 1), but be tailored, guided by ACCHSs, to their individual needs, including needs by remoteness. It will also be underpinned by current evidence such as national alcohol treatment guidelines,^10^ Alcohol Treatment Guidelines for Indigenous Australians^31^ and national alcohol consumption guidelines.^14^ The study methods will be based on principles of conducting health research with Indigenous Australians.^32^ This includes Indigenous involvement and engagement, benefits for Indigenous peoples, and led by Indigenous Australians.

**Table 1 T1:** Eight core support elements*

1	Service champions	Services asked to nominate two representatives to act as advocates of alcohol care and links between the service and research team
2	National workshop	National capacity building workshop for service champions at the start of the support phase (and for early support services, a wrap-up feedback workshop at the end of the maintenance support phase)
3	Onsite training	Training will be offered to each ACCHS at their service
4	Resources/funding	Some resources (eg, visual resources for brief intervention and clinical guidelines) will be given to services for free. Additional funding will be provided for the selection and purchase of further resources (eg, FASD doll, standard drink cups).
5	Practice software support	Support will be provided to services throughout the trial to facilitate the routine clinical use of alcohol-related items in the practice software.
6	Data feedback	Individual service data will be fed back to each service every second month
7	Phone conferences	Phone conferences will be held every second month between service champions and project team (including an addiction medicine physician). These will allow sharing of ideas and joint problem solving.
8	Online platform	Further resources and information will be shared via a secure online platform.

*These eight core elements of support will be tailored to local service needs. Further detail on each element is provided in the body of the text.

ACCHS, Aboriginal community controlled health service.

The primary outcome will be routinely collected data on screening rates using AUDIT-C. Secondary outcomes will include recorded delivery of brief intervention, counselling or prescribed medicines to reduce relapse in alcohol dependence. We will also describe changes in reported drinking and in biological measures that can be affected by drinking such as gamma glutamyltransferase (GGT, a liver enzyme),^33^ HbA1C^34^ and systolic blood pressure (BP).^34^

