### The model of support

ACCHSs will be acknowledged as the experts in cultural healthcare for Indigenous peoples in their communities and Australia. The study also recognises the need for flexibility based on needs of individual services and of the ACCHS sector as a specialist sector overall. Support approaches will include the same core elements (table 1). However, approaches will be tailored to the needs of each ACCHS, for what works best for their service, clients and communities.

The core support elements were designed based on evidence-based approaches for supporting implementation of alcohol care.^21 29^ The project team also drew on their experience working within (six authors) and with Aboriginal health services; and in health workforce development (nine authors). Advice was also received from ACCHS peak organisations and networks in New South Wales and South Australia, and from a research team conducting a quality improvement trial for ACCHSs on diabetes screening.^42^

At the start of the early support phase, the support will be refined based on preliminary analysis of qualitative data from staff interviews and after feedback from the initial national workshop for early support service representatives. Tailoring and further minor refinement of support will occur during the trial, informed by service feedback.

Early support (‘intervention’) services will receive the support soon after the trial starts (1 year of active support, 1 year maintenance phase). Late support (wait-control) services will receive the same intervention elements 2 years after the start of the early-support phase. Due to the nature of the intervention, it is not possible to blind participants or staff as to which services are receiving support.

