WorkshopsA national workshop will be held at the beginning of each support phase to bring champions from those services together for capacity building and networking. Feedback will be obtained from champions about pre/post-workshop knowledge, training preferences, priority areas for support and useful resources. Key presentations from workshops will be video-recorded and made available via a password-protected website.A wrap-up workshop will be organised for early support service champions (only) at the end of their support phase. Opportunities will be provided for service champions to provide verbal and written feedback on support, to discuss continuing quality improvement approaches and to network. Study results to that point will be discussed.Onsite trainingTraining will be offered at each service for all staff, with maximum duration of 2 days. Core elements will include screening, alcohol and the body, brief intervention and treatment approaches, including relapse prevention medicines. Due to the individuality of each service, flexibility will be given to allow inclusion of other (alcohol-related) training topics. The training will be co-facilitated by an addiction specialist (KC) and an Aboriginal researcher with clinical background ([name]) and will use culturally specific content and resources. Training content will be aligned with Indigenous protocols such as gender appropriateness, kinship systems and cultural obligations; such a family and community sharing which at times can impact on substance use.^27 44^ Pre/post-training feedback will be collected from participants.Resources/fundingThe trial will provide several hard copy and electronic resources for free to services (ie, the Handbook for Aboriginal Alcohol and Drug Work,^45^ Alcohol Awareness Kit^46^ and Quick Reference Guide to the Treatment of Alcohol Problems^47^).Each ACCHS will be provided with funding to purchase additional resources. Services can choose, in partnership with the chief investigators, how they spend their funding. The early support arm of the project will receive up to $9000 for resources. The late support arm will receive up to $3500. This is a reduced sum as they will have access to resources developed within the early support phase, so time and development costs will be less. Resources must be alcohol-related and may include additional training, conference attendance, education resources for staff or clients, funds for health promotion events or for local adaptation of resources.Practice software supportA Communicare support officer will be available during the trial to support ACCHSs with the practice software. Some ACCHSs may choose to make modifications to Communicare to make alcohol ‘clinical items’ more accessible for staff. One example is adding AUDIT-C into the Aboriginal and Torres Strait Islander (Indigenous) health assessment (‘Adult Health Check’), which was not routine in standard versions of Communicare at the time of trial commencement. AUDIT-C can also be added to other regular assessments such as antenatal and the pre-consult examination (ie, routine observations and/screening by a nurse or Aboriginal health worker before seeing the doctor). Services will also be provided with information about existing fields (‘clinical items’) available on Communicare for recording episodes of alcohol care (education/advice; on-site counselling), which can then be retrieved by data extraction.Second monthly data feedbackIndividual services will receive feedback on their routinely collected data on alcohol care every 2 months during their support phase. Data will be represented visually using images and or graphs (figure 3) and be fed back to nominated staff, including champions. Services will be asked for feedback on the data representation early in the support phase and adaptions will be made as requested. Services will be encouraged to discuss the results among staff, to see if there are ways to further improve alcohol screening and treatment rates.Phone conferencesSecond monthly phone conferences will be organised for service champions. These will provide the opportunity for ACCHSs to network nationally. The champions will be split into two groups for the phone conferences, based on remoteness. During teleconferences, champions can discuss their data feedback, progress, successes, difficulties, helpful tools, resources or approaches.Online platformA password-protected web portal will allow ACCHS staff to access and share current evidence, culturally appropriate resources and to network. It will include a discussion board. Short videos, training presentation slides and clinical protocols will be uploaded by project staff.

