### Patient and public involvement in the research

This trial was suggested by the Aboriginal Health Council of South Australia, the peak organisation for South Australian ACCHSs. Service participation in the trial must be approved by the board of each local ACCHS. The board is recognised as representing patients and community in such decisions. As described earlier, service staff will be consulted throughout their active support phase on how project support can best be tailored. Results will be fed back bimonthly to services in an accessible manner for all staff and board members, and services will have opportunity to provide comment on draft outcome reports before publication.

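### Practice software support is offered throughout the trial with no arm or phase limit, which conflicts with the care-as-usual wait-control and could dilute the contrast

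*Protocol article*

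**What the plan says.** The Overview sets the aim as testing a model of support "to increase the use of AUDIT-C and evidence-based treatment in ACCHSs compared with care as usual". The section on the model of support fixes the timing of the control arm: "Late support (wait-control) services will receive the same intervention elements 2 years after the start of the early-support phase".

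Table 1 lists practice software support as element 5 of the eight core elements and says: "Support will be provided to services throughout the trial to facilitate the routine clinical use of alcohol-related items in the practice software". The longer description under the model of support likewise makes a Communicare support officer available to the services for the duration of the trial. Neither place names an arm or a phase.

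The same description says what the help can involve. On screening: "One example is adding AUDIT-C into the Aboriginal and Torres Strait Islander (Indigenous) health assessment (‘Adult Health Check’), which was not routine in standard versions". This refers to the practice software as it stood when the trial began. On treatment: "Services will also be provided with information about existing fields (‘clinical items’) available on Communicare for recording episodes of alcohol care".

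Data feedback, by contrast, carries an explicit limit. Services receive "feedback on their routinely collected data on alcohol care every 2 months during their support phase".

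**The concern.** Element 5 is part of the package being tested, and it acts directly on what the trial measures. The primary outcome is AUDIT-C use as recorded in the practice software, and the treatment outcome depends on staff using extractable fields. The Discussion itself accepts that care entered as free text is not readily extracted. A template change or better use of the fields can therefore move the recorded outcomes without any other element being delivered.

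Read literally, the two descriptions of element 5 let a wait-control service ask for this help during its two control years. Such services have a reason to ask, because the Introduction notes that AUDIT-C became a national key performance indicator for these services in July 2017. Early use would raise recorded screening and treatment in the control arm and pull the estimated effect towards no difference. It would also blur two further planned analyses: whether the effect is replicated once the late arm is supported, and which elements of support were most effective.

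**Working it through.** **The passages side by side**

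- Comparator: care as usual (Overview).
- Timing in the control arm: the same elements, two years later (The model of support).
- Element 5: services, throughout the trial (Table 1); services, for the trial's duration (The model of support). The trial runs for 5 years, with data extracted from every service throughout (Quantitative data).
- Data feedback: only in the service's own support phase (The model of support).

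An element cannot be available to all services throughout and also be withheld from half of them for two years. The limit on data feedback shows that the authors state a phase limit elsewhere; element 5 has none in either place.

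**Reproducing the stated power**

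Inputs from the Sample size section: 10 services per arm, m = 86 unhealthy drinkers per service, ICC 0.04, 60% against 73%, two-sided 0.05, stated power 80%.

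- Design effect = 1 + (86 − 1) × 0.04 = 4.40.
- Effective n per arm = 10 × 86 / 4.40 = 195.5.
- Unpooled standard error = √[(0.60 × 0.40 + 0.73 × 0.27) / 195.5] = 0.0473. Power = Φ(0.13 / 0.0473 − 1.96) = 0.785.
- With the pooled variance under the null (SE₀ = 0.0477), power = Φ[(0.13 − 1.96 × 0.0477) / 0.0473] = 0.779.

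Both are close to the stated 80%, so the design has little reserve. A t reference with 18 degrees of freedom gives 0.739.

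**Illustrating dilution, for the treatment outcome only**

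Let f be the share of the 13-point effect that the control arm gains on average. It combines the part of the effect due to software support with the extent of early uptake; for example, half the effect in half the control services is f = 0.5 × 0.5 = 25%. The document gives no value for f, so a range is assumed. The control rate becomes 0.60 + 0.13f, the early arm stays at 0.73, and the pooled formula is used.

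| f (assumed) | Control rate | Difference | SE₀ | SE₁ | Power |
|---|---|---|---|---|---|
| 0 | 60.0% | 13.0 points | 0.0477 | 0.0473 | 0.78 |
| 10% | 61.3% | 11.7 points | 0.0475 | 0.0471 | 0.69 |
| 25% | 63.25% | 9.75 points | 0.0471 | 0.0469 | 0.54 |
| 50% | 66.5% | 6.5 points | 0.0465 | 0.0463 | 0.29 |

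Keeping the element within each service's own support phase corresponds to f = 0, the design as planned.

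**The case against.** The strongest reply is that this is loose wording. Timing by arm is set in the text on the model of support, and Table 1 only lists the contents of the package. Other rows, such as onsite training and phone conferences, also carry no arm or phase limit, and nobody would read them as reaching controls early. Element 5 may simply mean continuous help within a support phase, unlike a one-off workshop. Figure 2 (the flow diagram) and Figure 4 (the schedule) might settle the matter but are not visible here. Part of the remedy also exists already, since a spreadsheet will track when key elements reach each service.

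Much of this stands. The intention cannot be determined, and leakage follows only if control services actually use the help early. But element 5, unlike the other rows, states a duration, and that duration is the trial. The body text repeats it, so the conflict is in the text whatever was meant.

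Three stronger readings are tempting and are not supported:

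- **That feedback also leaks to controls.** The section on patient and public involvement says "Results will be fed back bimonthly to services in an accessible manner for all staff and board members", with no phase named. But the model of support already limits feedback to the support phase, and the preceding sentence in the involvement section concerns the active support phase.
- **That power for the primary outcome falls to the figures above.** They concern treatment provision. The Sample size section says that showing an increase in screening needs smaller numbers, so the loss on AUDIT-C is not quantified.
- **That the control condition is lost and the model goes untested.** Possible early access to one of eight elements does not show this. Because the bias is towards no difference, it would not by itself create a positive result.

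**Conclusion.** The point holds as a contradiction in the document with a known direction and an unknown size. As written, element 5 is open to wait-control services during the control period, contrary to the care-as-usual comparator and the two-year delay. If they use it, the contrast on AUDIT-C screening and on recorded treatment is diluted towards no difference.

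The power range of 0.69 to 0.29 illustrates sensitivity. It rests on an assumed average control gain of 10% to 50% of the effect, on the plan's own sizing inputs, and on an unchanged rate in the early arm. It is not a forecast. The plan should be corrected because the stated rule itself weakens the comparison, and the correction is small.

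**What to change.** Reconcile the passages. In Table 1 (element 5) and in the practice software paragraph under the model of support, limit the element to each service's own support phase. State that, before then, wait-control services receive only the technical help needed to run the data extraction. In the support-tracking spreadsheet already planned, record any alcohol-item or template change made in a wait-control service before its support phase, with its date, so that any contamination can be described when results are reported.

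If software help to both arms is deliberate, say so, and describe the comparator as usual care plus software support.

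The cost is a few words in two places and a column in an existing spreadsheet. The downside is that wait-control services get this help later, as they do the other elements.
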